#### Inclusion criteria

Eligible AYAs will: i) have finished cancer treatment for a primary or secondary/relapsed cancer with curative intent in the preceding 1–6 months; ii) be aged between 15–25 years (inclusive); iii) be able to read English; iv) be able to provide the name and contact details of a trusted health professional (e.g., local general practitioner, family doctor or hospital social worker); and v) be able to access the Internet in a private location (see also *Access Considerations* section below).

AYAs may also choose to invite a support person (a parent/caregiver, or spouse/partner) to take part in the study, although this is not a requirement of participation.

#### Exclusion criteria

AYAs will be excluded if during the initial intake interview they: i) have insufficient English language skills to complete the interview; ii) demonstrate extremely severe scores of depression (i.e., score > 28 on the Depression subscale of the Depression, Anxiety, Stress Scales-Short Form) 
[48] and/or endorse serious suicidal intent; or iii) endorse symptoms of psychosis or substance abuse.

If a participant relapses during the study period, they will be referred back to their treatment center for individual support, as their needs are likely to be difficult to manage in a group setting and can negatively affect others 
[49]. All excluded individuals will be referred to their treating centre for support.

#### Access considerations

Internet access and a suitable computer set-up is a requirement to participate in Recapture Life-AYA. This includes access to a computer/laptop which has a microphone and web-camera, and is located such that the participant will be able to participate in the sessions comfortably and in a private and uninterrupted capacity once per week for six weeks. AYAs without access to these resources will be able to borrow a laptop, web-camera, microphone and/or wireless internet connection device for the duration of the study (the costs of which are covered by a project grant). The equipment and internet needs of all AYA participants will be assessed at the initial telephone intake interview, and access issues managed on a case-by-case basis.

#### Participant recruitment

Potential participants aged ≥16 years will be mailed a personalised invitation letter, consent form and opt-in card by their oncologist. Parental consent to approach participants <16 years will be sought. Nominated support persons given the study information by their AYA child/partner may also choose to opt in by returning the consent form. The research assistant will contact all AYA participants who opt in to the study to request that participants sign and return a written contract agreeing to use the provided equipment solely for study purposes and to address internet access issues.

Recruitment will occur in 3x12 week blocks, such that ~80 patients who have completed treatment in the preceding 1–6 months will be invited 4 weeks prior to Week 1 of each block. This recruitment window was chosen to maximise the benefit to participants, by delivering the coping skills intervention early in survivorship. Given the assumed response and attrition rates (see above), it is envisaged that 3 iterations (i.e. 3x12 week blocks), each attracting ~40 AYA opt-ins, will be required to achieve the target sample. This means that 3 mail outs (approaching ~80 patients at a time) will occur for the study during 2012. This design ensures the standardisation of time since treatment completion across arms. All fully consented participants will be telephoned by the study co-ordinator one week prior to Week 1 to administer the Psychosocial Adjustment to Illness Scale (PAIS; T1 assessment). Participants will also complete the first online questionnaire at this time. (See Figure
1 below, for study flowchart).

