## Methods/Design

The Recapture Life-AYA study is a multi-site, phase II randomised controlled trial (RCT) to assess the feasibility and efficacy of a new, online, CBT-based intervention for AYAs after cancer treatment. AYAs aged 15–25 years at treatment completion will be recruited and randomised to one of three treatment arms: Recapture Life-AYA, a peer-support group (PSG) control, and a six week waitlist control group. The novel intervention, named **‘ReCaPTure LiFe-AYA’** (**R**esilience and **C**oping skills for young **P**eople and their families **T**o **L**ive well **F**ollowing cancer-**A**dolescent and **Y**oung **A**dult version), is delivered to groups of 3–5 AYAs by a psychologist in six, weekly online sessions, shortly after cancer treatment completion. The Recapture Life-AYA program is part of the larger Recapture Life program, which includes a Recapture Life-Parents/Carers program for caregivers of recently off-treatment paediatric cancer patients.

This study employs a 3 (treatment condition) x 3 (assessment point) factorial design. All participants will be assessed using a battery of measures at baseline (T1: recruitment), post-treatment (T2: seven weeks after T1) and 12 months following participation in Recapture Life-AYA or the PSG control (T3). These measures will include a measure of QoL, as well as measures assessing AYAs’ anxiety, depression, and family functioning.

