### Procedures

Following recruitment, participants will complete an intake interview with the study psychologist ([name]) to further screen for participant eligibility, orient participants to the study procedures, and ascertain the suitability of the participant’s internet connection. The intake interview will also serve to build rapport with the psychologist, by providing AYAs the opportunity to discuss their cancer experiences, current needs, and personal goals in participating in the study.

Participants will then be randomly allocated to one of the three study arms. The research assistant will send a hired (insured) laptop to any participants who do not have computer access two weeks before the commencement of each online group. This process will ensure equity (all participants will have access to identical equipment), minimise technical challenges (required software/hardware will be pre-installed) and will maximise security (security settings will be pre-set by the technical support person). All equipment will be returned after study participation. Participants randomised to the Recapture Life-AYA condition will also receive a written manual summarising the weekly home practice activities.

During Weeks 1–6 of each 12 week block, those allocated to Recapture Life-AYA and the PSG will participate in their allocated intervention. In Week 7, all participants will complete their second assessment (T2). For waitlist controls, this assessment will also serve as their T1 (pre-intervention) assessment. In Week 7, waitlist participants will be randomly allocated to either Recapture Life-AYA or PSG (completed during weeks 7–12). Waitlist participants will then complete a second T2 assessment, one week after their intervention.

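### The stated sequence implies that the T1 baseline follows random allocation; the order should be reconciled and T1 logged before allocation is run or disclosed

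*Protocol article*

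**What the plan says.** All references are to the protocol article.

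- **Participant recruitment.** Patients "will be invited 4 weeks prior to Week 1 of each block". On T1: "All fully consented participants will be telephoned by the study co-ordinator one week prior to Week 1", to give the PAIS, and "Participants will also complete the first online questionnaire at this time".
- **Procedures.** "Following recruitment, participants will complete an intake interview with the study psychologist". The next step is: "Participants will then be randomly allocated to one of the three study arms". The text then has laptops sent to those without computer access "two weeks before the commencement of each online group". The two active arms run in Weeks 1 to 6.
- **Methods/Design.** The first assessment is described as "baseline (T1: recruitment", with T2 seven weeks after T1.
- **Procedures, on T2.** "In Week 7, all participants will complete their second assessment (T2". For the waitlist this doubles as a new pre-intervention assessment. Re-allocation to one of the two programmes is described next, also in Week 7.
- **Table 1.** Intake and T1 are separate columns. The PAIS is marked at Intake only, whereas Participant recruitment makes it the T1 assessment.
- **Statistical analyses.** The contrasts are differences between groups in change in quality of life from T1 to T2 and from T1 to T3.

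**The concern.** A baseline is protected by randomisation only if it is fixed before participants can react to their allocation. Here the primary measure, the Impact of Cancer Scale, is completed online by the participants. Only the assessor is described as blind, and nobody can be masked to attending a weekly group rather than waiting. If T1 is answered after the arm is known, disappointment at waiting or anticipation of a group could move T1 differently between arms. That difference would enter the change from T1. The planned random-intercept model estimates the same change contrast and would not remove it.

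The laptop schedule could add to this. If dispatch follows the start of each participant's own group, a borrower in a Week 1 group receives equipment before T1 and a waitlisted borrower does not. Arrival of a laptop would then hint at the arm, and access to the online T1 could differ between arms.

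A baseline distorted in this way cannot be recovered after data collection.

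**Working it through.** **1. Reproducing the stated interval.** Number the weeks so that Week 1 = 1.

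| Event | Source | Week |
|---|---|---|
| Invitation | Participant recruitment: 4 weeks before Week 1 | 1 − 4 = −3 |
| Laptop dispatch, Week 1 groups | Procedures: 2 weeks before the group | 1 − 2 = −1 |
| T1 call and questionnaire | Participant recruitment: 1 week before Week 1 | 1 − 1 = 0 |
| Sessions, active arms | Procedures | 1 to 6 |
| T2 | Procedures | 7 |

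T2 − T1 = 7 − 0 = 7 weeks, which matches Methods/Design. If T1 were at the mail-out, the interval would be 7 − (−3) = 10 weeks. The recruitment label therefore cannot move T1 back to the invitation.

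**2. Placing allocation.** Procedures gives intake, allocation, dispatch in that order. Dispatch for Week 1 groups is at −1 and T1 is at 0. If the narrated order is the real order, allocation precedes T1 by at least about 0 − (−1) = 1 week. Timing dispatch to each online group also suggests that group membership is already known.

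**3. Other text that fits this order.**
- Randomization takes distress severity from the intake DASS-21, so allocation needs nothing from T1.
- Treatment fidelity has a co-ordinator, blind to allocation, give the pre-treatment measures and guess the condition at the start as well as the end. This fits an allocation that exists by T1, though it does not prove it.
- Access considerations places the assessment of equipment needs at intake. That puts intake before dispatch, and so before T1.

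**4. Text that points the other way.** T1 is labelled as recruitment. It is described in the recruitment section for all consented, not all randomised, participants. Procedures then places intake and allocation after recruitment.

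**5. Laptops for waitlist borrowers.** Their groups start in Week 7. The same two-week rule gives 7 − 2 = Week 5, well after T1 at Week 0.

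**6. What a shift at T1 would do (illustration only).** The documents give no size, so the values below are assumed. Let δ be the difference between two arms in T1 reporting caused by knowing the arm, in units of the pooled within-group SD used for d = 0.65. Let p be the share still present at T2. The error in the difference in change has size (1 − p)δ.

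| δ | p = 0: share of 0.65 | p = 0.5: share of 0.65 |
|---|---|---|
| 0.1 | 0.10/0.65 = 15% | 0.05/0.65 = 8% |
| 0.2 | 0.20/0.65 = 31% | 0.10/0.65 = 15% |
| 0.3 | 0.30/0.65 = 46% | 0.15/0.65 = 23% |

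At p = 1 the error is zero.

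The effect on a two-sided 5% test with no true difference uses n = 90/3 = 30 per arm (equal allocation is assumed, not stated) and p = 0. The false-positive rate is 1 − Φ(1.96 − δ√(n/2)) + Φ(−1.96 − δ√(n/2)), with √15 = 3.873. For δ = 0.1, 0.2 and 0.3 it is about 6.7%, 12.1% and 21.3%.

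**The case against.** The strongest reply is that no sentence dates allocation. Its position rests on the order of sentences in Procedures and on a laptop lead time. Laptops go to whoever lacks a computer, which is a criterion of need, not of arm. A schedule with dispatch by need two weeks before Week 1, T1 one week before, and allocation in the last few days would satisfy both stated lead times. Figure 1 may show exactly that, and it is not available here.

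This stands as far as it goes: the order is implied, not stated. That schedule would, however, put allocation after the dispatch that Procedures describes as following it, and equipment timed to each group would leave before groups were formed. The text would still need correcting.

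A reader might infer more: that participants already know their arm at T1, and that every primary contrast is biased one-for-one. The documents do not support this.

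- No passage says when participants learn their allocation.
- A shift passes in full only if it has gone by T2; whatever persists cancels.
- Recapture Life and the peer-support group share platform, facilitator, group size, frequency and session length, so disappointment at waiting does not separate those two arms.
- The shift sizes are assumptions, and the direction is unknown.

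Nor is Week 7 shown to be in the wrong order. The text gives T2 first and re-allocation second; it does not say that one must be logged before the other is run.

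**Conclusion.** The concern holds as an implied order that needs correcting. Followed as written, Participant recruitment and Procedures put T1 about a week or more after allocation, while Methods/Design labels T1 as recruitment. That exposes an unblinded, self-reported primary baseline to knowledge of the arm, mainly in the comparisons with the waitlist.

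The bias cannot be sized from the documents. The range of 15% to 46% of d = 0.65 rests on assumed shifts of 0.1 to 0.3 SD that have wholly gone by T2; if half persists, it is 8% to 23%. The conclusion on order rests on reading the Procedures narrative as a sequence. If the flowchart or the full protocol puts T1 first, what remains is a contradiction in the text. It should be settled before a block recruits, because the remedy is cheap then and unavailable later.

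**What to change.** 1. Reconcile Methods/Design, Participant recruitment, Procedures and Table 1 on the order of intake, T1 and allocation, and on whether the PAIS belongs to Intake or T1.
2. Require the T1 questionnaire and the PAIS to be completed and logged before randomisation is run. Failing that, require that allocation is not disclosed until T1 is logged, and say so.
3. Time laptop dispatch so that it cannot reveal the arm before T1, for example by sending to all borrowers on one schedule ahead of T1.
4. State that waitlist T2 is logged before the Week 7 re-randomisation is run.

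**Cost.** This reorders contacts that are already planned. T1 may fall one to two weeks earlier in all arms, so the seven-week T1–T2 interval would become about 8 to 9 weeks (7 + 1 to 7 + 2) and must be restated. Borrowers may need equipment earlier or telephone completion of T1. If only disclosure is delayed, T1 can stay where it is, but equipment and session arrangements must be made without signalling the arm.

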**Figure 1 F1:**
[figure not shown]
Recapture Life-AYA study flowchart.

### Randomization

Participants will be randomised to one of the three study arms: a) Recapture Life-AYA, b) the PSG, or c) a waitlist condition. A flexible biased urn method of randomization, will be used, which adapts to the degree of imbalance between groups in a dynamic manner over the trial 
[50]. This method is superior to standard stratification in balancing groups across multiple covariates 
[51,52] whilst also being a suitable method when groups remain small 
[50,53,54]. This minimization will be based on four factors: (i) gender (male/female), (ii) severity of distress as measured by the Depression, Anxiety, Stress Scale-Short Form (DASS-21) intake interview (see below), (iii) time since treatment, classified into two groups, and (iv) degree of rural/remoteness as assessed by the Accessibility/Remoteness Index of Australia 
[55]. Participants will be randomised using electronic randomization used by independent personnel at the University of New South Wales.

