### Participants

This study will recruit 90 AYA participants from hospitals across Australia in the first 1–6 months after treatment completion. AYAs will also have the option of inviting a support person to receive information and updates through the Recapture Life-AYA study, however as this is optional no ‘target’ sample size of support persons has been set. The AYA sample size will allow differences of a medium to large effect size (*d* = 0.65, the difference in change from T1 to T2 for any pair of groups, standardised on the pooled within-group standard deviation) on the primary outcome variable (QoL) to be detected with a power of 80% at a significance level of 0.05 (two-tailed). This effect size is clinically significant 
[42] and is based on other RCTs of similar interventions for AYAs with chronic illness 
[43-45]. It is anticipated that approximately 220 patients will need to be approached to achieve a final sample of 90 participants (assuming a response rate of 50% and attrition rate of 20%, based on previous interventions with AYA) 
[19,46,47].

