### Interventions

#### Recapture Life-AYA intervention

Recapture Life is guided by the *Adolescent Resilience Model* (ARM) 
[56]. Based on extensive research in AYAs with cancer, the ARM conceptualises resilience in young people as a multifaceted process, involving the interaction of individual, family and social-level risk and protective factors to determine AYAs level of resilience, and ultimately their quality of life. Additional file 
1: Table S1 identifies the key components of this model and the way in which these processes are targeted in Recapture Life. Several adaptive processes are implicated by this model including AYAs’ ability to: enact positive coping behaviours, negotiate uncertainty in illness and cancer-related distress, reappraise the experience in order to derive adaptive meaning from it, and seek and maintain support from family and friends. To our knowledge, only one other published intervention has utilised this framework in AYAs 
[57,58], however this music therapy intervention is delivered individually to AYAs receiving stem-cell transplants whilst on treatment. As such, this program may not offer the skill-building and peer support that we hypothesise are crucial to promote adaptation into survivorship. In addressing these component processes of resilience after cancer, our manualised program derives its core mechanisms of change from CBT techniques.

The primary goals of the Recapture Life-AYA intervention are to improve QoL, reduce distress and facilitate healthy coping in young cancer survivors. Participants randomised to Recapture Life-AYA will participate in six, weekly, 90-minute sessions facilitated by a psychologist. Each group will comprise the psychologist plus a minimum of 3 and a maximum of 5 AYAs with mixed diagnoses and genders, separated into two age groups: 15–17 and 18–25 years. Each Recapture Life-AYA module applies CBT techniques to the key domains of concern identified by our team’s previous work 
[59,60] (See Additional file 
2: Table S2).

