One challenge inherent in the design of this study will be to quantify the effect of support person (e.g., parent/caregiver) participation on AYA psychological outcomes. Parents/caregivers may have an important role in assisting AYAs to negotiate the disruption cancer causes in their normal trajectory toward independence 
[91]. Parent inclusion in skills-based programs also appears to increase their likelihood of improving AYA psychological outcomes 
[29]. However, in this trial the decision was made to make parent/support person participation optional, to facilitate and support the autonomy and independence of the AYA participants. This design may result in greater statistical complexity when attempting to delineate the impact of parental/support person involvement in AYA interventions.

Despite its strengths, the study design also has methodological vulnerabilities. The three-armed design of this trial, while a strength on the one hand, is also likely to increase the time it takes to recruit sufficient participant numbers. In addition, our decision to divide AYA participants into two defined age groups (15–18 and 19–25 years) may increase the time between recruitment and actual group participation.

The long-term, 12-month follow-up is another aspect of the study design that, although methodologically important, may add complexities to final data analyses. Participants may differ markedly in terms of the psychosocial support services they receive in this time, and the number of other AYA cancer survivors they come into contact with. Individual differences in terms of additional support services and peer support is a factor that is likely to be important throughout the trial as a whole. All of these factors will require careful monitoring and documentation, and will need to be taken into account in data analyses and interpretation.

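### Age band fixes which therapy group a participant can join, yet it is not a minimisation factor, its cut-point is defined in two ways, and the expected waitlist is too small for four age-split groups at Week 7

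*Protocol article*

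**What the plan says.** All references are to the protocol article.

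- **Randomization:** "This minimization will be based on four factors". The four are gender, DASS-21 distress, time since treatment and remoteness.
- **Recapture Life-AYA intervention:** each group has "a minimum of 3 and a maximum of 5 AYAs with mixed diagnoses and genders", "separated into two age groups: 15–17 and 18–25 years". The peer-support group (PSG) section applies the same group size and a two-way age split to the control.
- **Discussion:** the bands differ here. The authors describe a decision to "divide AYA participants into two defined age groups (15–18 and 19–25 years") and say that it may lengthen the wait before a group starts.
- **Procedures:** the active arms run in Weeks 1–6 of each 12-week block, and everyone has T2 in Week 7. Then "In Week 7, waitlist participants will be randomly allocated to either Recapture Life-AYA or PSG", to be completed in Weeks 7–12.
- **Participants and Participant recruitment:** "This study will recruit 90 AYA participants from hospitals across Australia in the first 1–6 months after treatment completion". About 220 are to be approached, "assuming a response rate of 50% and attrition rate of 20"%. There are three blocks, each with about 80 invited and about 40 opting in.

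**The concern.** A participant can be treated only in a group of the right intervention and the right age band. Each block therefore has four intervention-by-age cells to fill, and a cell of 1 or 2 falls below the stated minimum. The allocation balances four other characteristics and leaves this one to chance. The conflicting cut-point adds to the problem, because 18-year-olds change the size of both cells.

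The powered comparison is the T1-to-T2 change between arms, with T2 set at Week 7. If an undersized group waits for more members, its participants either reach T2 before finishing six sessions or are assessed on a different clock from the waitlist. At Week 7 the waitlist is divided again, individually, into the same four cells, and there is little room for delay because delivery must fit Weeks 7–12.

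**Working it through.** **Reproducing the plan's recruitment figure.** 90 / (0.50 × 0.80) = 225, against about 220 stated. This agrees within 3%, so 90 is the number left after attrition.

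**Waitlist supply per block** (the allocation ratio is not stated; 1:1:1 assumed):
- From the final target: 90 / 3 blocks / 3 arms = 10.
- From 40 opt-ins after 20% attrition: 40 × 0.80 / 3 = 10.7.
- From 40 opt-ins before attrition: 40 / 3 = 13.3.

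The documents do not say how much attrition falls before Week 7, so 10 to 13 is the range.

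**Share in the younger band.** The documents give no age distribution. If ages are even over the 11 years from 15 to 25, the 15–17 band is 3/11 = 0.27 and the 15–18 band is 4/11 = 0.36. These are assumptions; 0.20 and 0.50 are shown as a wider range.

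**First phase, age not balanced.** Any count of 3 or more can be divided into groups of 3 to 5, so the problem counts are 1 and 2. With n per arm, the younger count Y in an arm is Binomial(n, p). Let q be the probability that neither Y nor n − Y equals 1 or 2. The chance of at least one undersized cell across the two active arms is 1 − q².

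Example, n = 10 and p = 3/11: q = 0.582, so 1 − 0.582² = 0.66.

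**First phase, age band balanced.** The block's younger total is Binomial(3n, p), spread as evenly as possible over three arms with any remainder placed at random. This is a best case, since a biased urn working on five factors will balance age less than perfectly.

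| Younger share | 10 per arm: unbalanced → balanced | 13 per arm: unbalanced → balanced |
|---|---|---|
| 0.20 | 0.82 → 0.83 | 0.69 → 0.57 |
| 0.27 | 0.66 → 0.51 | 0.44 → 0.19 |
| 0.36 | 0.40 → 0.15 | 0.18 → 0.02 |
| 0.50 | 0.20 → 0.01 | 0.04 → 0.00 |

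**Week 7.** Running both interventions in both bands needs 2 × 2 × 3 = 12 people.
- With 10 or 11 waitlisted, the probability of four groups of at least 3 is 0.
- With 13 and simple 1:1 re-randomisation (multinomial over four cells), it is 0.005 to 0.07 for younger shares of 0.20 to 0.50. With 13 forced into arms of 6 and 7, it is 0.01 to 0.17.
- Allowing empty cells, so that fewer than four groups run and nobody is left in a group of 1 or 2, the probability with 10 under simple re-randomisation is 0.05 to 0.32 for younger shares of 0.50 down to 0.10.
- With age balanced and each band split evenly, four groups need at least 6 in each band. The probability is still 0 with 10 or 11, and 0.10 to 0.42 with 13 (shares 0.27 to 0.50).

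**The case against.** Several objections have force.

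- **A reader might infer that therapy groups cannot be formed at all.** The documents do not support that. The figure of 10 comes from a post-attrition target, and 40 opt-ins give about 13 per arm, above 12. Nothing says that all four cells must run in every block, and with an empty cell 10 people can sometimes be placed in viable groups.
- **A reader might infer that participants would be switched to the other arm to fill a group.** No section suggests this. The only consequence the authors name is delay.
- **The Discussion already discloses delay.** This stands as an acknowledgement. It does not settle the matter, because Procedures fixes T2 at Week 7 and waitlist delivery in Weeks 7–12.
- **The first-phase risk depends on an assumed age mix.** It does: at an even split it falls to 0.20 or 0.04.
- **The article is condensed.** A rule for undersized groups, or the balancing used at Week 7, may stand in the full protocol, so their absence is not counted here. The list of four factors and the two age definitions, by contrast, are stated in the text.
- **Allocating each waitlist age band as a whole might seem to solve Week 7 with two groups.** It does not. With a maximum of 5, ten people fit two age-band groups only on an exact 5/5 split (8% of blocks at a 0.27 share, 25% at 0.50), and thirteen never fit. It would also tie age to treatment within the block.

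**Conclusion.** The concern holds in a limited form. Age band governs group membership in both interventions but is not among the four minimisation factors, and its definition conflicts between the intervention section and the Discussion. The conflict rests on no assumption.

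Under equal allocation and 27–36% in the younger band, the chance per block of at least one active-arm age cell of 1 or 2 people is about 0.40–0.66 with 10 per arm and 0.18–0.44 with 13. At Week 7, individual re-randomisation into four cells cannot give four groups of at least 3 with 10–11 people and is unlikely to with about 13, though fewer groups may sometimes run.

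The Week-7 conclusion is much less sensitive to the age mix than the first-phase one. It concerns a secondary phase; the first-phase risk bears on the timing of the powered T1-to-T2 comparison.

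**What to change.** 1. Reconcile the age bands in the Recapture Life-AYA intervention section and the Discussion, so that one definition applies throughout.
2. Add that age band as a fifth minimisation factor. At 27–36% in the younger band, the first-phase risk falls to about 0.15–0.51 (10 per arm) or 0.02–0.19 (13 per arm) if balance is ideal. At a 20% share with 10 per arm there is no gain. The cost is one more factor in the electronic randomisation, with slightly weaker balance on the other four.
3. Reconcile the Week-7 re-randomisation in Procedures with the 3-to-5 group size and the 10–13 waitlisted people expected per block. Step 2 does not remove this shortfall. The cost is a short clarification in the text.
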